**3. TRIAL DESIGN**

**3.1. Statement of the endpoints**

- **Primary endpoint**

The primary endpoint will be the proportion of participants who complete the assigned treatment regimen, defined as: 1) 90 doses within a maximum of 16 weeks, without interruptions longer than 2 weeks, and no more than on 2 occasions, for the 3HR arm (control); 2) 12 doses within a maximum of 14 weeks, without interruptions longer than 10 days, for the 3HP arm (experimental 1), and 3) 120 doses within a maximum of 20 weeks, without interruptions longer than 2 weeks, and no more than on two occasions, for the 4R arm (experimental 2).

- **Secondary endpoints**
- Proportion of participants who definitively discontinue the assigned treatment because of adverse events, regardless of its relationship to the treatment of the study.
- Proportion of participants who definitively discontinue the assigned treatment because of adverse events related to the treatment of the study.
- Crude mortality: Number of participants who die while on the study, regardless of its relationship to investigational medicinal products (IMPs) of the study.

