**3.3. Randomization**

Eligible patients who fulfil the inclusion criteria will be randomly assigned to one of the three study arms. Randomization will be stratified for sites and for 3 subgroups according to the renal substitutive therapy (non-dialysis, on haemodialysis, or on peritoneal dialysis), in a 1:1:1 allocation ratio, using a computer-generated randomization list integrated into the Research Electronic Data Capture (REDCap) platform.

- **3HR arm (control).** Consists of three months of daily isoniazid (5 mg/Kg) plus rifampin (10 mg/Kg).
- **3HP arm (experimental 1).** Consists of three months of once-weekly isoniazid (15 mg/Kg) plus rifapentine (900 mg for ≥50 Kgs or 750 mg for 32 to 50 Kgs).
- **4R arm (experimental 2).** Consists of four months of rifampicin (10 mg/Kg).

**3.4. Description of the treatment** (for detailed information, see **Section 5** **“TRIAL INTERVENTION” section**)

- **Isoniazid**

Isoniazid is the hydrazide of isonicotinic acid and is one of the primary drugs for tuberculosis treatment. The activity of isoniazid is limited to the mycobacteria of the *M. tuberculosis* complex. It is bactericidal for rapidly dividing organisms and bacteriostatic for “resting” bacilli. The mechanism of action is the inhibition of the biosynthesis of mycolic acids, a component of the mycobacterial cell wall. It is approved in Spain for the treatment of active and latent TB.

Isoniazid will be part of two arms of the study: in combination with rifampicin (control arm) and combined with rifapentine (experimental 1 arm). In the control arm, participants will receive 5 mg/Kg (up to 300 mg) of isoniazid, administered daily, for three months (90 doses). In the experimental 1 arm, participants will receive isoniazid 900 mg weekly, combined with rifapentine, for 12 weeks.

- **Rifampicin**

Rifampicin is a semi-synthetic rifamycin derivative that is highly active against mycobacteria, most gram-positive bacteria, and some gram-negative bacteria. It is bactericidal for both intracellular and extracellular microorganisms. By inhibiting prokaryotic DNA-dependent RNA polymerase, it suppresses the early elongation of the nucleotide chain in RNA synthesis.

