**8. STATISTICAL METHODS**

**8.1. Statistical analysis**

The efficacy analysis will be performed on the modified intention-to-treat population, which will consist of all randomized subjects. The proportions of participants who completed the assigned treatment in the 3HR arm (control) will be compared with the proportions in either 3HP arm (experimental 1) or 4R arm (experimental 2). Since renal replacement therapy could have a potential influence on medication tolerance, especially INH, and thus could influence outcome, the analysis for the primary endpoint will be performed for the population as a whole and by subgroups (non-dialysis, on haemodialysis, or on peritoneal dialysis).

For safety, analyses will be performed on all randomized subjects who have received at least one dose of the assigned study treatment. Likewise, proportions of permanent discontinuation of the assigned treatment, related and unrelated to the study medication, and death, in the control arm will be compared with either experimental arm.

Statistical analyses will be performed by two investigators of the Biostatistics Unit of the IDIBELL, who will remain unaware of the trial-group assignments until the analyses have been completed. Differences between arms will be tested by Student’s t-test, if normally distributed, or a Wilcoxon two-sample test, if not normally distributed, or by chi-square analysis for categorical variables. Whenever possible, estimators will be given 95%CI. Statistical significance was set at a p-value <0.025. Treatment of the data and analysis will be performed with the statistical package R, version 3.4.1 or superior.

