**8.2. Sample size**

The sample size has been calculated to demonstrate a clinically significant better completion with the 3HP or 4R regimens than the 3HR regimen. With an α= 0.025, β= 0.20, and 5% expected losses, and assuming a 0.75 proportion of treatment completion in the control arm (3HR), according to our previous experience, 225 subjects (75 per arm) will be needed to demonstrate, if exists, a 0.16 increase in treatment completion rates in the experimental arms (4R or 3HP) respectively. Sample size was calculated with GIGAcalculator (<https://www.gigacalculator.com/calculators/power-sample-size-calculator.php>).

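### Randomisation is stratified by site and renal replacement therapy, but the only test named for the primary proportion is a plain chi-square: valid, slightly conservative, and cheap to improve

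*Protocol*

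**What the plan says.** - Protocol 3.3: "Randomization will be stratified for sites and for 3 subgroups according to the renal substitutive therapy", "in a 1:1:1 allocation ratio". The therapy groups are non-dialysis, haemodialysis and peritoneal dialysis.
- Protocol 3.1: "The primary endpoint will be the proportion of participants who complete the assigned treatment regimen". The primary endpoint is therefore binary.
- Protocol 8.1, on why the therapy groups matter: "Since renal replacement therapy could have a potential influence on medication tolerance, especially INH, and thus could influence outcome". The analysis that follows from this "will be performed for the population as a whole and by subgroups (non-dialysis, on haemodialysis, or on peritoneal dialysis").
- Protocol 8.1, on tests: one sentence covers all variables, with a t-test or Wilcoxon test for continuous data, "or by chi-square analysis for categorical variables". It mentions no strata, covariates or model. Site does not appear in the analysis at all.
- Protocol 8.1, on the threshold: "Statistical significance was set at a p-value <0.025". Sidedness is not stated.
- Protocol 8.2: "With an α= 0.025, β= 0.20, and 5% expected losses", with completion of 0.75 in the control arm, an increase of 0.16, and 75 per arm.

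**The concern.** Stratified allocation balances the arms on replacement therapy, so differences between the therapy groups add almost nothing to the chance difference between arms. A plain chi-square still counts those differences in its variance. If therapy predicts completion, the standard error is too large, the test rejects too rarely under the null, and some power is lost.

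The protocol gives its own reasons to expect therapy to matter. Section 1 links dialysis to isoniazid neurotoxicity, and section 5.4 lists neurotoxicity as a ground for definitive discontinuation, which counts as non-completion under 3.1.

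The subgroup analyses do not fill the gap. They leave the overall comparison unadjusted, and separate tests within therapy groups do not test whether the effect differs between them.

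What is at stake is efficiency, in a trial with no power to spare.

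**Working it through.** **1. The plan's own figure.** With p0 = 0.75, p1 = 0.91 and mean 0.83, the pooled formula is n = [z_a √(2 × 0.83 × 0.17) + z_b √(0.75 × 0.25 + 0.91 × 0.09)]² / 0.16², where the two roots are 0.5312 and 0.5190.

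- Two-sided 0.025: (2.2414 × 0.5312 + 0.8416 × 0.5190)² / 0.0256 = 103.5, so 104 per arm, or 110 after 5% losses.
- One-sided 0.025: (1.960 × 0.5312 + 0.8416 × 0.5190)² / 0.0256 = 85.3, so 86 per arm, or 91 after losses.
- The stated 75 per arm is not reproduced. With 75 analysed per arm, power is 64.6% two-sided or 74.7% one-sided.

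That is a separate point. It sets the baseline here.

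**2. Why the plain test is conservative.** Under the null its variance per patient is p(1−p) = 0.75 × 0.25 = 0.1875. Under balanced strata the true value is the weighted mean of the within-stratum p(1−p). The actual two-sided error is 2[1 − Φ(2.2414/√r)], where r is the ratio of the second to the first. The documents give no stratum shares or rates, so these are assumptions: shares of 30/50/20% and three sets of rates, rounded to two decimals.

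- Moderate, 0.86/0.69/0.75: 0.3 × 0.1204 + 0.5 × 0.2139 + 0.2 × 0.1875 = 0.1806; r = 0.963; error 0.022.
- Strong, 0.94/0.63/0.77: 0.3 × 0.0564 + 0.5 × 0.2331 + 0.2 × 0.1771 = 0.1689; r = 0.901; error 0.018.
- Very strong, 0.97/0.59/0.82: 0.3 × 0.0291 + 0.5 × 0.2419 + 0.2 × 0.1476 = 0.1592; r = 0.849; error 0.015.

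**3. Simulation.** One pairwise comparison, 75 per arm, two-sided 0.025, overall rates held at 0.75 and 0.91, arms balanced within strata, 20,000 runs per scenario. CMH is the Cochran-Mantel-Haenszel test on the randomisation strata.

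| Assumed strata | Type I, chi-square | Type I, CMH | Power, chi-square | Power, CMH |
|---|---|---|---|---|
| Therapy, not prognostic | 0.025 | 0.024 | 65.2% | 65.2% |
| Therapy, moderate | 0.022 | 0.023 | 66.0% | 66.9% |
| Therapy, strong | 0.018 | 0.024 | 66.0% | 68.8% |
| Therapy, very strong | 0.015 | 0.025 | 66.6% | 71.1% |
| Moderate therapy, 5 differing sites | 0.021 | 0.024 | 66.7% | 68.0% |
| Strong therapy, 5 strongly differing sites | 0.013 | 0.025 | 66.9% | 72.9% |
| Not prognostic, 10 sites (30 strata) | 0.025 | 0.022 | 66.1% | 64.3% |

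A second set of 100,000 runs used therapy strata of 26/38/11 per arm. Type I error was 0.022, 0.017 and 0.014 for the plain test and about 0.024 to 0.025 for the stratified test. The power gains were about 1, 3 and 6 points. The most extreme case used control rates near 0.95/0.70/0.40, shifted so that the average is 0.75 (unshifted it is 55.7/75 = 0.743). Its power was about 66% against 72%.

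**4. Interval width.** In the second set the stratified interval was about 3 to 9% narrower. As a large-sample check on the first set, take the root of the summed within-stratum variances of both arms over 0.1875 + 0.0819 = 0.2694. The experimental-arm rates are 0.95/0.88/0.91, 0.98/0.86/0.93 and 0.99/0.85/0.95.

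- Moderate: √[(0.1806 + 0.0834)/0.2694] = 0.990.
- Strong: √[(0.1689 + 0.0791)/0.2694] = 0.960.
- Very strong: √[(0.1592 + 0.0762)/0.2694] = 0.935.

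That is about 1 to 6.5% narrower. Part of the larger simulated figure arises because the usual stratum-wise variance runs slightly small in strata of this size, so the low end is the safer guide.

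**5. Subgroups.** An equal split gives 225/9 = 25 per arm per therapy group. For 0.75 against 0.91 at two-sided 0.025, exact chi-square power is about 5% with 11 per arm, 24% with 25 and 37% with 38.

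**The case against.** The sentence on tests is generic. It covers every variable, does not say that the test is unstratified, and a Cochran-Mantel-Haenszel test is itself a chi-square test. A statistical analysis plan that is not shown could name one, and adjustment, site pooling and interaction tests are often left to it. This keeps the point minor, but it does not turn the sentence as written into a stratified analysis. Section 8.1 names both a test and a use for the therapy groups, and that use is subgroup analysis only.

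The gain also rests on inputs that the documents do not give. The protocol says only that therapy could matter, and large gains need very different completion rates between groups. This stands, which is why the size is given as a range starting at zero.

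A reader might infer more than the documents support in four ways:

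- That the planned test is invalid or biased. It is not: its false-positive rate stays at or below nominal, and balanced allocation leaves the risk difference unbiased.
- That stratifying makes up the missing power. In these scenarios it stays well below 80%.
- That stratifying can never cost anything. With 30 sparse, non-prognostic strata it lost about 2 points.
- That the protocol claims its subgroup tests will show effect modification. It promises only an analysis by subgroup.

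**Conclusion.** The point holds as a minor one: the analysis does not use the strata that the design imposed. The cost is efficiency only. Under the assumed shares and rates, a test stratified by replacement therapy gains 0 to 1 point of power if therapy is weakly to moderately prognostic and about 3 to 6 points if strongly so. The plain test's type I error is about 0.022 down to 0.014 instead of 0.025.

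These figures assume 75 analysed per arm, a two-sided 0.025 threshold and the protocol's 0.75 against 0.91. The direction does not depend on the assumed strata, provided that they are prognostic and not very sparse. The size does. The sample-size shortfall has to be dealt with separately.

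**What to change.** In section 8.1:

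- For each comparison with 3HR, make the primary test Cochran-Mantel-Haenszel stratified by replacement therapy, and report a Mantel-Haenszel (stratum-weighted) risk difference with its confidence interval.
- Include site only with small sites pooled under a rule set in advance, because very sparse site-by-therapy strata can cost 1 to 2 points of power.
- Report risk differences by therapy group descriptively, with intervals and without separate significance claims. One treatment-by-therapy interaction test per comparison is optional and should be labelled as low-powered.

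The cost is a wording change in the protocol, carried into the analysis plan. Site and therapy group are already needed for randomisation, so no further data are required. The change should be made before the analysis, so that the choice of test does not depend on the results.

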**2. OBJECTIVES AND PURPOSE OF THE TRIAL**

- **Primary objective**

To determine if treatment completion with either three months of once-weekly isoniazid plus rifapentine (3HP) or four months of daily rifampicin (4R) or both is better in comparison to three months of daily isoniazid plus rifampicin (3HR) for treatment of latent TB infection in patients with end-stage kidney disease.

- **Secondary objective**

To determine the safety and tolerability of a 3HR, 3HP, and 4R regimens for the treatment of latent TB infection in patients with end-stage kidney disease.

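### Section 8.1 tests at p<0.025 but reports 95% intervals; if 0.025 is the two-sided share of 0.05 for two comparisons, the two primary differences need 97.5% intervals

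*Protocol*

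**What the plan says.** Two adjacent sentences in protocol section 8.1 fix the interval level and the test threshold: "Whenever possible, estimators will be given 95%CI. Statistical significance was set at a p-value <0.025". Categorical variables are to be compared by chi-square, which covers the primary endpoint (treatment completed or not).

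Section 2 lets the trial succeed on either experimental regimen or on both. It asks whether 3HP or "four months of daily rifampicin (4R) or both is better in comparison to three months of daily isoniazid plus rifampicin (3HR"). Section 8.1 accordingly compares the control arm with each experimental arm.

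Section 8.2 uses the same threshold for planning: "With an α= 0.025, β= 0.20, and 5% expected losses", "assuming a 0.75 proportion of treatment completion in the control arm (3HR"), and "a 0.16 increase in treatment completion rates in the experimental arms (4R or 3HP) respectively". The result is that "225 subjects (75 per arm) will be needed to demonstrate" this.

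Neither section says whether 0.025 is one- or two-sided, names an overall error rate, or explains why 0.025 was chosen.

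**The concern.** A confidence interval and a test agree only when their levels correspond. A two-sided test at 0.025 corresponds to a 97.5% interval. A 95% interval corresponds to a two-sided test at 0.05, or to a one-sided test at 0.025.

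The 0.025 reads most naturally as 0.05 divided by two comparisons, because there are exactly two comparisons against one control and the usual 2×2 chi-square p-value is two-sided. On that reading the threshold has been adjusted for multiplicity and the interval has not. A primary comparison with p between 0.025 and 0.05 would be declared not significant while its interval lies wholly on one side of zero. Readers of the trial report could then take either message from the same result.

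**Working it through.** **Inputs.** From section 8.2: control completion 0.75, increase 0.16 (so 0.91), alpha 0.025, power 0.80, losses 5%, 75 per arm. From section 8.1: threshold 0.025, 95% intervals, chi-square. From sections 2 and 8.1: two comparisons sharing one control, allocated 1:1:1 (section 3.2), so the two test statistics have correlation of about 0.5 under the null hypothesis. The side is not stated, so both are shown.

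**1. Can the sample size reveal the side?** The pooled two-proportion formula, with mean proportion (0.75 + 0.91)/2 = 0.83, is

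n = [z_α·√(2·0.83·0.17) + 0.8416·√(0.75·0.25 + 0.91·0.09)]² / 0.16²

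- One-sided 0.025 (z = 1.960): (1.0412 + 0.4368)² / 0.0256 = 85.3, so 86. With losses, 86/0.95 = 90.5, so 91 per arm.
- Two-sided 0.025 (z = 2.241): (1.1907 + 0.4368)² / 0.0256 = 103.5, so 104. With losses, 104/0.95 = 109.5, so 110 per arm.

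The stated 75 per arm is not reproduced on either side, so section 8.2 does not settle which was meant. The shortfall itself is a separate matter.

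**2. Two-sided reading: multiplicity.** The two levels sum to 0.025 + 0.025 = 0.05. Family-wise error is 1 − P(|Z₁| < 2.241 and |Z₂| < 2.241). With correlation 0.5 this is 1 − 0.9535 = 0.0465. A simulation with 75 per arm, a shared control and 1,000,000 replicates gives 0.047. The two overall comparisons are controlled at two-sided 5%.

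**3. Two-sided reading: interval against test.** Take 56/75 completers on control and 66/75 on an experimental arm.

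- Uncorrected chi-square = 4.39, p = 0.036: not significant at 0.025.
- Difference = 10/75 = 0.133. Standard error = √(0.7467·0.2533/75 + 0.88·0.12/75) = 0.0627.
- 95% interval: 0.133 ± 1.960·0.0627 = 0.010 to 0.256, which excludes zero.
- 97.5% interval: 0.133 ± 2.241·0.0627 = −0.007 to 0.274, which includes zero and agrees with the test.

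**4. How often this happens.** Same simulation settings, with both experimental arms at 0.91:

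| Quantity | Result |
|---|---|
| p between 0.025 and 0.05, one comparison | 0.109 |
| p ≥ 0.025 with Wald 95% interval excluding zero, one comparison | 0.111 |
| At least one of the two comparisons in the p zone | 0.20 |

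**5. Joint coverage of the two intervals** (bivariate normal, correlation 0.5): 0.909 for two 95% intervals and 0.954 for two 97.5% intervals.

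**6. One-sided reading.** The critical value is 1.960, so the 95% interval matches the test. Family-wise error is 1 − P(Z₁ < 1.960 and Z₂ < 1.960) = 0.045, one-sided. That is above the conventional one-sided 0.025 and below one-sided 0.05.

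**7. Cost in width.** 2.241/1.960 = 1.144, so intervals are about 14% wider.

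**The case against.** The strongest reply is that section 8.1 defines significance by the p-value alone. The interval sentence is general: it covers single-arm proportions, safety and subgroup estimates as well. Unadjusted 95% intervals beside an adjusted threshold are then a presentation choice, and p = 0.036 is simply not significant. It is true that the decision rule is not ambiguous on the two-sided reading, and that 95% intervals are acceptable for secondary estimates. But nothing in section 8.1 exempts the two primary differences or labels their intervals as unadjusted, and those are the estimates on which the report will be read.

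A second reply is that the side of a test is often left to the SAP, which is not shown here. That is fair, and the missing side alone is not the finding. The stated pairing of 0.025 with 95% is.

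A reader might also infer a dilemma: either the intervals contradict the tests, or the two comparisons are uncontrolled and the false-positive rate nearly doubles. The protocol does not support that. On the best-supported reading multiplicity is controlled. On the one-sided reading the 4.5% is an excess only over an overall one-sided 2.5%, which the protocol never states. An intended overall one-sided 5% would leave tests and intervals in agreement and the two comparisons covered.

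**Conclusion.** The point holds in a limited form. If 0.025 is the two-sided Bonferroni share of 0.05, the 95% level is wrong for the two primary differences and should be 97.5%. At the design's own effect and 75 per arm, the mismatch would show in about 11% of trials per comparison and about 20% for at least one. Joint coverage of the two intervals is about 91%.

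This rests on three assumptions: chi-square p-values are two-sided, both experimental arms truly reach 0.91, and all 75 per arm are analysed. The protocol does not state the first, although the test and the value 0.025 point to it. The false-positive rate, the estimates and the significance decisions are unaffected on this reading; what is affected is how a primary result is displayed and understood. It should be corrected, and it is a small correction.

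**What to change.** In section 8.1, state that tests are two-sided with family-wise alpha 0.05 over the two primary comparisons, 0.025 each. Report 97.5% intervals for the two primary risk differences. Keep 95% intervals for secondary, safety and subgroup estimates, labelled as unadjusted for multiplicity. The cost is two or three sentences and primary intervals about 14% wider; conduct and data collection do not change. If the sponsor meant one-sided tests, section 8.1 should say so and name the overall level.

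An optional alternative, which corrects no error, is Holm: the smaller p-value against 0.025 and, if that is met, the other against 0.05. It keeps the same family-wise level and is never less powerful. With 75 per arm and both experimental arms at 0.91, power to succeed on both rises from 0.51 to 0.63, and per-arm power from 0.656 to 0.715. If only one arm reaches 0.91, that arm's power moves only from 0.656 to 0.657.

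Holm should not be combined with 97.5% intervals without explanation. The second comparison could be significant at 0.05 while its 97.5% interval includes zero, in about 0.63 − 0.51 = 12% of trials when both arms reach 0.91. If Holm is chosen, state that the 97.5% intervals are the simultaneous intervals and that the Holm-adjusted p-value decides significance.

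### Optional improvement: testing the two primary contrasts by Holm instead of at a fixed 0.025 would raise power to show both regimens better, at the same family-wise bound

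*Protocol*

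**What the plan says.** The primary objective (protocol, section 2) asks whether "either three months of once-weekly isoniazid plus rifapentine (3HP) or four months of daily rifampicin (4R) or both is better" than 3HR, so there are two contrasts with a shared control and three possible positive answers. Section 1 gives the working hypothesis that both regimens will be better tolerated and better completed.

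Section 8.1 compares control completion with each experimental arm, names chi-square for categorical variables, and sets a single threshold: "Statistical significance was set at a p-value <0.025". It asks for 95% confidence intervals where possible. It describes no step-down.

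Section 8.2 uses the same level, "With an α= 0.025, β= 0.20, and 5% expected losses", and concludes that "225 subjects (75 per arm) will be needed to demonstrate, if exists, a 0.16 increase in treatment completion rates". Allocation is "in a 1:1:1 allocation ratio" (section 3.3).

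The protocol does not say whether 0.025 is one- or two-sided, does not call it a share of 0.05, and does not state a family-wise error rate.

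**The concern.** Two contrasts each tested at two-sided 0.025 amount to a single-step Bonferroni split of 0.05. Once one regimen has been shown better at 0.025, the other can be tested at 0.05 without the family-wise error exceeding 0.05. Under the rule as written, a second regimen with a p-value between 0.025 and 0.05 is reported as not shown better, although the same error bound would allow the claim. The loss is largest when both regimens work, which is what the protocol hypothesises.

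Because 8.1 states the decision rule, an analysis plan that tested the second contrast at 0.05 would depart from the protocol. The natural place for the change is therefore 8.1.

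**Working it through.** **Inputs.** From section 8.2: control completion 0.75; increase 0.16, so 0.91; level 0.025; power 0.80; losses 5%; 75 per arm. From section 3.3: equal allocation. From section 8.1: chi-square test and p<0.025. Evaluable per arm after losses: 75 × 0.95 = 71.25, taken as 71.

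**The plan's own figure.** Pooled formula for two proportions, with mean proportion (0.75 + 0.91)/2 = 0.83:

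n = [z_α √(2 × 0.83 × 0.17) + z_β √(0.75 × 0.25 + 0.91 × 0.09)]² / 0.16²

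The square roots are 0.5312 and 0.5190, and z_β = 0.8416.

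- Two-sided 0.025 (z = 2.2414): (1.1907 + 0.4368)² / 0.0256 = 103.5, so 104 per arm, or 110 with 5% losses.
- One-sided 0.025 (z = 1.9600): (1.0412 + 0.4368)² / 0.0256 = 85.3, so 86 per arm, or 91 with losses.

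The stated 75 does not reproduce on either reading. At 75 per arm the same formula gives power per comparison of 0.646 (two-sided) or 0.747 (one-sided), against 0.80 stated.

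**The two rules.**

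- Fixed: each contrast is positive if its p<0.025. Family-wise error is at most 0.025 + 0.025 = 0.05.
- Holm: the smaller p is tested against 0.025; if significant, the larger is tested against 0.05. If neither regimen differs from control, a false rejection needs the smaller p to be below 0.025, the same event as under the fixed rule. If exactly one does not differ, a false rejection needs that contrast's p to be below 0.05. The bound is 0.05 in both cases.

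Holm rejects everything the fixed rule rejects, and sometimes more.

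**Size of the gain.** Simulation of 2,000,000 three-arm trials with a shared control, uncorrected chi-square and two-sided p-values:

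| Completion (3HR, and the two experimental arms) | n per arm | Quantity | Fixed | Holm |
|---|---|---|---|---|
| 0.75, 0.91, 0.91 | 75 | both shown better | 0.509 | 0.627 |
| | 75 | one given contrast | 0.656 | 0.715 |
| | 75 | at least one | 0.804 | 0.804 |
| 0.75, 0.91, 0.91 | 71 | both shown better | 0.469 | 0.592 |
| 0.75, 0.91, 0.85 | 75 | both shown better | 0.209 | 0.299 |
| 0.75, 0.91, 0.75 | 75 | both shown better (one falsely) | 0.012 | 0.024 |
| 0.75, 0.75, 0.75 | 75 | any rejection | 0.047 | 0.047 |

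Consistency check for equal effects: P(both) = 2 × P(one given) − P(at least one). Fixed: 2 × 0.656 − 0.804 = 0.508. Holm: 2 × 0.715 − 0.804 = 0.626. Both agree with the table to rounding. With a continuity-corrected chi-square (200,000 simulated trials) the figures for both are 0.422 and 0.528, a similar gain.

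**If 0.025 is one-sided** (75 per arm, 0.91 in both experimental arms):

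| Rule | Both | At least one |
|---|---|---|
| Fixed, one-sided 0.025 each | 0.644 | 0.886 |
| Holm, one-sided family-wise 0.05 | 0.751 | 0.886 |
| Holm, two-sided family-wise 0.05 | 0.627 | 0.804 |

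Holm still gains about 11 points for both if the family level is one-sided 0.05. Against a one-sided fixed rule, the two-sided wording loses on both measures.

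**The case against.** The fixed rule is valid, simple and conservative, and choosing it over a step-down is a legitimate preference. That stands. A reader might infer that 8.1 is wrong or fails to control error. The document does not support this, since the error bound is met.

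The protocol never says that 0.025 is a share of 0.05. The pairing with 95% intervals suits a one-sided 0.025 test and does not match a two-sided one. This stands as a real ambiguity. In favour of the two-sided reading, an ordinary chi-square p-value is two-sided, and two contrasts at 0.025 add to 0.05. But the text does not settle it, and the value of two-sided wording depends on the answer.

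A reader might also infer that the trial loses power it promised for the joint conclusion. It promised none: section 8.2 is sized for "a 0.16 increase in treatment completion rates in the experimental arms (4R or 3HP) respectively", that is, for each contrast separately. On that target Holm gains about 6 points (0.656 to 0.715), still below 0.80.

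Finally, Holm might be taken as a remedy for the sample size. It is not, because the first rejection still has to be made at 0.025 and the chance of at least one positive result does not move.

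**Conclusion.** This is an optional, inexpensive improvement and not an error. If p-values are two-sided and the intended family-wise level is 0.05, Holm adds about 12 points of power to show both regimens better (0.51 to 0.63 at 75 per arm; 0.47 to 0.59 at 71 evaluable) and about 6 points per comparison, with no change in the family-wise bound. The main figures assume 0.75 in the control arm, 0.91 in both experimental arms and an uncorrected chi-square. With a second regimen at 0.85 the gain for both is 9 points, from a low base of 0.21.

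The recommendation depends on the sponsor stating the sidedness and family-wise level of 0.025. The shortfall of 75 per arm against 80% power is a separate and weightier matter that this change leaves in place.

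**What to change.** In section 8.1, first say what 0.025 is. If it is the two-sided share of a family-wise 0.05, add for the primary endpoint: *The two primary comparisons are tested by the Holm procedure at a two-sided family-wise level of 0.05: the smaller p-value is compared with 0.025 and, if it is significant, the larger with 0.05. Decisions are read from the Holm-adjusted p-values.* The adjusted values are 2 × p(smaller), and the greater of that and p(larger), each capped at 1 and compared with 0.05.

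If 0.025 was meant one-sided, state the family-wise level and apply Holm at that level and sidedness instead of using the sentence above.

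The cost is a short amendment to the text, made before any comparative results are seen, with no added patients or data. There are two downsides. The interval for the second-ranked contrast may not match the Holm decision: a 97.5% interval can include zero when Holm rejects, and a 95% interval can exclude zero when Holm does not. And if only one regimen works, the chance of wrongly claiming both rises from 0.012 to 0.024, still within the bound. The sample size should be reconsidered separately.
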